## Materials and methods

### Study design, eligibility, and recruitment

This is a multi-institutional prospective, observational cohort study of patients electing to undergo either ESS or continued medical therapy (CMT) for CF-related CRS after having failed initial medical therapy. Patients will be enrolled at one of nine participating CF centers across the US.

Potential participants will be considered for study inclusion if they are adults (age 18–99 years), diagnosed with CF by genetic testing and/or sweat chloride testing, and have persistent CRS based on multi-disciplinary guidelines [5, 6]. Patients who underwent ESS in the 12 months preceding study enrollment, plan to have follow-up care at a non-participating institution, are unable to complete post-operative outcome measures, or started or modified new CFTR modulator therapy within 90 days of study enrollment will be excluded **(Table 1).** Participants consenting to study will be included in one of two study groups: those who elect to undergo ESS and those who pursue CMT. Extent of surgery, including use of extended approaches, will be tracked and analyzed.

**Table 1 pone.0310986.t001:** Inclusion and exclusion criteria.

Inclusion Criteria	Exclusion Criteria
Age 18 years or older	Underwent ESS in past 12 months
Diagnosed with CF as established by genetic testing combined with clinical assessment and/or sweat chloride	Will obtain follow up care at nonparticipating institutions
Diagnosed with CRS by multidisciplinary sinusitis guidelines	Unable to complete outcome measures
CRS symptoms persisting beyond initial medical treatment	Started new CFTR modulator therapy less than 90 days prior to screening or anticipated to begin during study period

ESS, endoscopic sinus surgery; CF, cystic fibrosis; CRS, chronic rhinosinusitis, CFTR, cystic fibrosis transmembrane receptor

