### Objectives & endpoints

Objective 1: Determine whether ESS outperforms CMT for CF-related CRS over 12 months follow-up using endpoints of percent of predicted expiratory volume in the first second (ppFEV_1_), the rate of pulmonary exacerbations (PEx), and antibiotic utilization for exacerbations.Objective 2: Delineate changes in QOL and sinus-related comorbidities for participants who undergo ESS through 12 months of follow-up compared to CMT. Endpoints include assessing the impact of treatment on CF-specific QOL, CRS-specific QOL, sleep quality, depression, headache, cognition, and olfaction, which will be assessed using validated patient-reported outcome measures.Objective 3: Define changes in productivity loss (PL) and health utility value (HUV) in PwCF+CRS who undergo ESS through 12 months follow-up compared to standard CMT. Endpoints are validated patient-reported outcome measures to quantify PL and HUV.

All objectives will also evaluate the impact of ESS compared to CMT on pulmonary, rhinologic, QOL outcomes accounting for HEMT. Objectives and endpoints are listed in **Table 2**.

**Table 2 pone.0310986.t002:** Study objectives and endpoints in prospective observation study in adults with cystic fibrosis and comorbid chronic rhinosinusitis.

Objective	Endpoint	Assessments
1) Determine whether ESS outperforms CMT for CF-related CRS using measures in pulmonary function, the rate of PEx, and antibiotic use in over 12 months follow-up	Change in percent of predicted expiratory volume in the first second (ppFEV_1_) at initial visit and months 3,6,9, and 12.	NA
	Rate of PEx, and antibiotic utilization for exacerbations compared between treatment groups.	
2) Delineate changes in CF-specific quality of life and sinus-related comorbidities for subjects who undergo ESS through 12 months of follow-up and assess if ESS outperforms CMT in these areas.	Descriptive summary of CF-specific QOL, CRS-specific QOL, sleep quality, depression, headache, cognition, and olfaction; and improvement in scores and comparisons between groups from baseline through 12 months post-treatment.	CFQ-R (CF QOL), SNOT-22 (CRS QOL), PSQI (Sleep), PHQ-9-revised (Depression), HIT-6 (Headache), CFQ (Cognitive function), QOD (Olfaction), SIT (Smell Identification Test)

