### Statistical methods

For all objectives, we will verify predictive model assumptions and test goodness-of-fit, considering alternative models if needed. We will account for potential site-specific differences as fixed effects in our models. Other methods to address site clustering include mixed effects models and generalized estimating equations.

For Objective 1, mixed effects model will be used to assess the impact of ESS versus CMT on ppFEV_1_ changes at initial and subsequent visits. Fixed effects will include baseline FEV1 (FEV1 > 80% predicted, <80% and > 50%, and <50%), CF variant status, use of CFTR modulator therapy, sex, prior sinus surgery, time and treatment; patients will be treated as random effects. An unstructured variance approach will model within-subject errors, and we will explore other covariance if needed. As exploratory analysis, we will compare ppFEV_1_ from a year before enrollment to post-treatment values using the same model. Using a generalized linear model with a Poisson distribution and prior year data, we will assess the impact of ESS versus CMT on exacerbation rates and antibiotic use, complemented by descriptive statistics for sociodemographic factors.

For Objective 2, we will describe patient characteristics using summary statistics. Treatment effects on patient reported-outcome measures (CFQ-R, SNOT-22, PHQ-9, PSQI, CFQ, QOD, and SIT) will be explored via a mixed effects model, adjusting for multiple comparisons using a gate-keeping procedure and assessing for self-report bias in patient-reported outcomes by comparing them to FEV1.

For Objective 3, we will correlate productivity costs with patient demographics, disease factors, pulmonary status, and QOL impairment. We will use a mixed effects model to evaluate these outcomes.

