Additionally, we will implement multiple approaches to compare changes in longitudinal treatment outcomes listed in objectives 1–3 between the ESS and CMT groups. First, multivariate Profile Analysis (MPA) [30], unlike the mixed model approach, can handle multiple variables simultaneously and does not require stringent assumptions. Two main effects from the MPA model are of interest: 1) Tests on patient group differences at baseline on the outcomes in the study and 2) tests of “parallelism”, determining if the outcome trajectories (or profiles) change similarly in the two patient groups over time. Second, we will apply Propensity Score Matching (PSM) to test for the causal effects of ESS and CMT on study outcomes, and to create balanced treatment comparisons to address self-selection biases [31, 32]. Other methods using propensity scores like weighting or stratification, and instrumental variable (IV) approach, will also be considered to adjust for potential biases and estimate causal effects.

Consideration was given to restricting enrollment to surgically naïve patients; however, this approach would limit enrollment. We will therefore explore subgroup analyses in surgically naïve study participants and sensitivity analyses to look at changes over time in outcomes. We also plan to account for surgical history in a mixed effects model that includes previous sinus surgery.

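### As listed, the Objective 1 mixed model analyses the pre-treatment visit but has no treatment-by-time term, so its treatment coefficient is an averaged level difference, not an effect on change

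*Protocol article*

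**What the plan says.** The Outcome assessments section makes ppFEV1 the primary pulmonary outcome. For Objective 1, Statistical methods says a "mixed effects model will be used to assess the impact of ESS versus CMT on ppFEV_1_ changes at initial and subsequent visits". Table 2 (Objectives & endpoints) gives the endpoint as "Change in percent of predicted expiratory volume in the first second (ppFEV_1_) at initial visit and months 3,6,9, and 12", so the initial visit is one of five analysed time points.

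The listed fixed effects begin with baseline FEV1 in three bands, cut at 80% and 50% predicted, then CF variant status, modulator use and sex, and end with "prior sinus surgery, time and treatment; patients will be treated as random effects". On covariance, the section adds: "An unstructured variance approach will model within-subject errors".

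Groups form by patient choice: "those who elect to undergo ESS and those who pursue CMT" (Study design, eligibility, and recruitment).

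Later in Statistical methods, a multivariate profile analysis with a parallelism test, and propensity-score matching, are introduced as further approaches. Profile analysis is said to be one that "can handle multiple variables simultaneously and does not require stringent assumptions". The section on patient retention and missing data makes the mixed model, fitted by full information maximum likelihood, the primary analysis.

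**The concern.** When treatment is chosen and not randomised, the groups may differ before anything is done. The evidence for ESS is then the difference in how the groups change. A model with time and treatment as separate main effects, fitted to data that include the pre-treatment visit, has no parameter for that. It gives one group difference for all visits.

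Two things follow for the primary pulmonary outcome. The pre-treatment visit, where there can be no effect, pulls the estimate towards the baseline difference. And any baseline gap that three wide bands fail to absorb enters the coefficient and can pass for benefit, or hide it. The initial value is also used twice, as a response and, banded, as a covariate.

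**Working it through.** **Inputs from the article.** Five visits, one of them pre-treatment; the fixed effects above; two-sided 5% level; 80% power for a 1.6-point ppFEV1 change (2.3 accounting for HEMT) with 170 participants and 20% dropout. **Not in the article, so assumed:** SDs, correlations, group split and baseline gap.

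**1. The plan's own figure.** 170 × 0.8 = 136 completers. With a 1:1 split, the SD of change that makes 1.6 detectable is 1.6 / [(1.960 + 0.842) × √(4/136)] = 1.6 / 0.480 = 3.33. With all 170 analysed it is 3.72. For 2.3 points the values are 4.79 and 5.35. No SD is stated, so the figure can be neither confirmed nor refuted. It does show that the quantity powered is a change.

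**2. What the listed model estimates.** Write the mean at visit j as μ + τ(j) + β·ESS + covariates. The ESS-CMT difference is β at every visit, including the first, so the modelled difference in change from the initial visit is β − β = 0.

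Suppose the true difference is g at the initial visit and g + δ(j) afterwards. With covariance matrix S and no baseline covariate, β is estimated as g + Σ w(j)δ(j), with weights w = S⁻¹1 / (1′S⁻¹1). For a constant δ = 1.6 and g = 0:

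| Covariance | Weight on pre-treatment visit | Coefficient for a true 1.6 |
|---|---|---|
| Compound symmetry | 0.20 | 1.28 |
| 0.85 shared + 0.15 AR(0.5) | 0.29 | 1.14 |
| AR(0.95) | 0.47 | 0.86 |

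Under compound symmetry a constant 3 becomes 0.8 × 3 = 2.4. An effect rising linearly to 3 at month 12 becomes (0 + 0.75 + 1.5 + 2.25 + 3)/5 = 1.5. Its post-baseline mean is 7.5/4 = 1.875, so most of that shortfall from 3 comes from averaging over visits and only the step from 1.875 to 1.5 from the pre-treatment visit.

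**3. Simulation with the three bands included.** Both settings assume a between-patient SD of 20. Setting A: 60 v 60, visit SD 5, 4,000 data sets. Setting B: 68 v 68, SD of change 3.33, 100 data sets.

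| Setting | Baseline gap (ESS − CMT) | True effect | Listed model: estimate | Listed model: rejection |
|---|---|---|---|---|
| A | 0 | 3 | 2.40 | 26% |
| A | −5 | 3 | 1.22 | – |
| A | −5 | 0 | −1.20 | 10% |
| B | 0 | 1.6 | 1.55 | 15% |
| B | −5 | 1.6 | 0.09 | 6% |
| B | +5 | 0 | +1.03 | 10% |
| B | −10 | 0 | −2.22 | 27% |

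The share of the gap left by the bands is (2.40 − 1.22)/5 = 0.24 in A, and 2.22/10 = 0.22 and 1.03/5 = 0.21 in B, so roughly a fifth to a quarter. The B row with no gap does not itself show dilution: its Monte Carlo error is about 1.57/√100 = 0.16, so 1.55 is compatible with both 1.28 and 1.6. The algebra and setting A carry that point.

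**4. With a treatment × post-baseline term.** In B, a true 1.6 is estimated as 1.59 (gap 0) and 1.55 (gap −5), with rejection 97% and 93%; under a true 0, rejection is 2–5%. The SE is 0.45 against 1.59 for the main-effect coefficient, a ratio of 3.5, because a level difference keeps between-patient variation that a change removes. In A, power for 3 points is 65% for a month-12 comparison and 85% for a post-baseline average, both adjusted for continuous baseline.

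**The case against.** The article says the fixed effects will include these terms, so the list is open; site effects are mentioned outside it. A condensed article may leave an interaction to an analysis plan that is not shown. That stands, and a reader should not infer that the investigators have ruled an interaction out.

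It can also be said that the outcome is worded as ppFEV1 changes with baseline as a covariate, which suits a model of post-baseline change. In such a model a treatment main effect is the average effect on change. But both Statistical methods and Table 2 put the initial visit among the analysed visits, where change is zero by construction. The text as it stands does not describe that model.

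The baseline-difference and parallelism tests and propensity-score matching do address differential change and self-selection. They lessen the harm, but they are presented as additions. Matching could shrink the baseline gap; it would not remove the dilution.

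Three stronger inferences are tempting and are not supported:

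- **That the bias always hides a benefit.** A gap in the other direction inflates the estimate.
- **That a patient random effect on top of an unstructured residual covariance invalidates the analysis.** The two are redundant if both are fitted, but the fixed-effect estimates do not change. The wording may only name the clustering unit.
- **That profile analysis will discard a known share of patients.** The article states neither its implementation nor the missingness per visit, so no count can be given.

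**Conclusion.** The point holds for the model as written. With the initial visit in the response and no treatment-by-time term, the treatment coefficient is an averaged level difference. This is more than an omitted detail, because the terms that are stated do not estimate the change the article says it will assess and powers for.

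The direction of the problem follows from the algebra alone. The size does not: 20% dilution of a constant effect rests on compound symmetry, five equally weighted visits and no baseline gap. The simulated biases, rejection rates and power figures rest on assumed SDs, equal groups and chosen gaps. They illustrate the problem and do not predict this study's results. Nothing here shows the 1.6-point figure to be wrong.

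**What to change.** Choose one of two specifications for Objective 1:

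1. Keep all five visits as response, add treatment × visit with visit categorical, drop the baseline bands, and pre-specify one ESS-minus-CMT difference in change from baseline. Either month 12 or the average over months 3–12 is defensible; the choice must be made in advance.
2. Model months 3–12 only, with continuous baseline ppFEV1 as covariate. With self-selected groups and a noisy baseline this keeps a small bias (about −0.3 points at a 5-point gap under setting A), so option 1 is somewhat safer.

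Either way, use the baseline value as response or as covariate, not both. The exploratory comparison with the year before enrolment is to use the same model and should be reworded to match.

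Two minor wording points. State one covariance specification: unstructured residual, or random intercept with a structured residual. Remove or qualify the statement on profile analysis, which in its classical form assumes multivariate normality, a common covariance matrix and complete profiles.

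The cost is wording in the analysis plan; no new data are needed. The Current status section reports enrolment continuing, with 87 participants as of October 2023.

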### Evaluation timeline

The following information will be collected at the patient’s initial consultation visit and 3, 6, 9, and 12 months follow-up with +/- 4-week ranges for follow up time points. These time points were selected based on the prior frequency that people with CF had routine clinic visits before the regulatory approval of ETI, as the study was designed in 2018.

Pulmonary function testing data that was obtained as clinical standard of care based on clinical records to analyze ppFEV1.PEx-related medical history and diagnostic testing; and data regarding utilization of oral and IV antibiotic utilizationQuestionnaires: Cystic Fibrosis Questionnaire-Revised (CFQ-R), 22-question Sino-Nasal Outcome Test (SNOT-22; © Washington University, St. Louis, MO), Pittsburgh Sleep Quality Index (PSQI), Patient Health Questionnaire-9-revised (PHQ-9-revised), Cognitive Failures Questionnaire (CFQ), and Headache Impact Test (HIT-6)Evaluations for olfactory function: 40-question Smell Identification Test (SIT; © Sensonics International, Haddon Heights, NJ) and the Questionnaire of Olfactory Disorders (QOD) for olfactory specific QOL assessmentProductivity loss and health utility data: Work Productivity and Activity Impairment-Specific Health Problem (WPAI) and 5-dimensional EuroQol questionnaire (EQ-5D-5L; © EuroQol Group, Rotterdam, The Netherlands) to quantify health utility value.

Mucus and nasal microbiome samples

A set of questions on attitudes regarding sinusitis will be completed once at the baseline visit. Data collection time points are identical for both ESS and CMT subjects and are further detailed in **Table 3.**

**Table 3 pone.0310986.t003:** Data collection time points in months.

Data collection time points	Baseline	3	6	9	12
History and physical, computed tomography	x				
Disease and socio-demographic factors	x				
Nasal endoscopy	x		x		
Treatment option: ESS vs. CMT	x				
Medication, CFTR modulator, cross-over data	x	x	x	x	x
PFTs, PEx data, antibiotic use	x	x	x	x	x
CFQ-R, SNOT-22, QOD, PSQI, PHQ-9-revised, CFQ, SIT, HIT-6, WPAI, HUV	x	x	x	x	x
Nasal mucus sponge, nasal microbiome swab	x	x	x	x	x
Blood, excised ethmoid sinus tissue*	x				

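### The main ppFEV1 model takes its pre-treatment level from one enrolment visit and leaves prior-year ppFEV1 exploratory, so a deeper enrolment dip among ESS electors could pass as an ESS effect

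*Protocol article*

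**What the plan says.** The Objective 1 endpoint in Table 2 (Objectives & endpoints) is "Change in percent of predicted expiratory volume in the first second (ppFEV_1_) at initial visit and months 3,6,9, and 12", so there is one pre-treatment measurement. Spirometry is routine-care data: "Pulmonary function testing data that was obtained as clinical standard of care based on clinical records to analyze ppFEV1" (Evaluation timeline).

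Under Statistical methods, a "mixed effects model will be used to assess the impact of ESS versus CMT on ppFEV_1_ changes at initial and subsequent visits". The fixed effects are enrolment FEV1 in three bands (above 80, 50 to 80, and below 50 percent predicted), then "CF variant status, use of CFTR modulator therapy, sex, prior sinus surgery, time and treatment; patients will be treated as random effects". No prior-year level or slope is listed.

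Prior-year ppFEV1 has one role: "As exploratory analysis, we will compare ppFEV_1_ from a year before enrollment to post-treatment values using the same model". The next sentence gives the prior year a place in the named exacerbation and antibiotic analysis: "Using a generalized linear model with a Poisson distribution and prior year data".

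The same section also plans profile analysis and propensity score matching, with weighting, stratification or an instrumental variable as alternatives, to deal with self-selection.

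**The concern.** Groups form by patient choice after initial medical therapy has failed, and no criterion in Table 1 requires stable lung function at the enrolment visit. Suppose ESS electors are, on average, further below their own usual level at that visit than CMT electors. They then recover more over the following months with no treatment effect at all, and the model credits the difference to ESS.

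Adjusting for enrolment FEV1 does not help, because two patients with equal enrolment values can have different usual levels when one of them is in a dip. The same holds for matching on enrolment ppFEV1, which is the only ppFEV1 value among the predictors under Baseline measures. The parallelism test in the profile analysis starts from the same visit, so a rebound appears there as non-parallel profiles.

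At stake is the primary pulmonary outcome, for which the plan aims at an effect of 1.6 points.

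**Working it through.** **1. The plan's own figure.** Statistical power and sample size gives 170 participants, 20% dropout, 80% power, two-sided 5% and a detectable 1.6 points. It gives no SD, correlation or allocation ratio, so the figure can only be inverted. Assuming 1:1 allocation, 170 × 0.8 = 136, or 68 per arm.

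SD of change = 1.6 / [(1.960 + 0.842) × √(2/68)] = 1.6 / 0.480 = 3.33, which implies a test-to-test SD of 3.33/√2 = 2.35.

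**2. Bias after adjusting for continuous enrolment ppFEV1.** Let B be the between-patient SD, W the independent test-to-test SD, δ the extra dip in ESS electors, and k the number of prior-year values averaged, all taken before the dip. With no true effect, the false ESS gain is

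δ / (1 + k + W²/B²).

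With B = 20 and δ = 2 (both assumed):

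| k | W = 4 | W = 5 | W = 6 |
|---|---|---|---|
| 0 (enrolment value only) | 1.92 | 1.88 | 1.83 |
| 1 | 0.98 | 0.97 | 0.96 |
| 2 | 0.66 | 0.65 | 0.65 |
| 4 | 0.40 | 0.40 | 0.39 |

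Example: k = 0, W = 5 gives 2 / (1 + 25/400) = 2 / 1.0625 = 1.88. The bias is proportional to δ: zero at δ = 0, 0.94 at δ = 1, 2.82 at δ = 3 (k = 0, W = 5).

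**3. Simulation of the planned forms.** 3,000 runs, 68 per arm, B = 22, no true effect, a 2-point dip in ESS only. W is 2.35 (matching step 1) or 4.

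| Analysis | False gain, W = 2.35 / 4 | False-positive rate |
|---|---|---|
| Change from enrolment, three bands | 1.98 / 1.96 | 93% / 52% |
| 12-month value, continuous enrolment value | 1.98 / 1.95 | 94% / 52% |
| 12-month value, three bands | 1.58 / 1.58 | 14% / 13% |
| Treatment main effect over all visits including enrolment, three bands | 1.19 / 1.18 | 11% / 11% |
| 12-month value, continuous enrolment plus mean of four prior values | 0.39 / 0.42 | 12% / 9% |
| Change from mean of four prior values | 0.00 / 0.03 | 5% / 5% |

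Several forms are shown because the article lists time and treatment but no treatment-by-time term. With the same 2-point dip in both arms, every form gave no bias and a false-positive rate of about 5%.

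**4. Precision (illustrative).** For one follow-up value, residual variance is W² × [1 + 1/(1 + k + W²/B²)]. At W = 5 and B = 20 the residual SD is 6.97 with the enrolment value only, and 6.09, 5.76 and 5.47 with k = 1, 2 and 4. For k = 1 the variance ratio is 48.5/37.1 = 1.31, worth about 31% more patients; for k = 4 it is 48.5/29.9 = 1.62.

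**5. Can a differential dip be seen?** The difference enrolment minus prior-year mean has SD W√(1 + 1/k). With 85 per arm, the difference detectable at 80% power is 2.80 × W√(1 + 1/k) × √(2/85). This is 1.1 points at W = 2.35, k = 4, but 3.0 points at W = 5, k = 1.

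**The case against.** The strongest reply is that the bias is conjectural. Recruitment is from otolaryngology clinics for persistent sinus symptoms, not for a fall in lung function; both groups meet the same criterion; and a shared dip cancels. All of this stands. It limits the claim to a risk that the main model does not guard against. The formula is symmetric, so a deeper dip among CMT electors would bias against ESS.

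A reader might infer that the prior-year analysis is only an uncontrolled before-and-after look. The text does not support that. It uses the same model, which contains treatment, so it is already a between-group comparison anchored before enrolment and a useful partial check. What it lacks is a stated role in the interpretation.

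The propensity methods also count. The article does not give a closed list of score variables, and leaving that to a fuller document is no fault. The point is only that matching on enrolment ppFEV1 would not remove a dip.

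Test SDs of 4 to 6 do not fit the change SD of 3.33 implied by the 1.6-point target. That is fair, and it makes the precision gains illustrative. The bias barely depends on the SD: it is 1.98 at the plan-implied value.

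The contrast with the exacerbation model is weak evidence of inconsistency, since a rate needs a look-back period and ppFEV1 has a measured baseline. Finally, Table 3 lists no prior-year spirometry. That such values will be obtained is inferred from the exploratory sentence and the use of clinical records, and their number per patient is unknown.

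**Conclusion.** The concern holds as a conditional one. The main ppFEV1 model rests on one self-selected enrolment visit, and the planned adjustments do not remove a differential dip at that visit. An assumed 2-point difference leaves about 1.9 points on change from enrolment, and one of about 1.6 points would produce the whole effect that the study is powered to detect. Under readings of the model that do not target change from enrolment, the false gain is 1.2 to 1.6.

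These sizes assume a dip that recovers fully, independent test errors, prior values taken before the dip, no underlying decline and 1:1 allocation. Serially correlated errors would shrink the benefit of adding prior values. A reader might go further and infer that the planned analysis will favour ESS. The article does not support that, because it gives no evidence that lung function at enrolment is depressed more in one group than in the other.

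**What to change.** - In the Objective 1 model, enter enrolment ppFEV1 as a continuous covariate instead of three bands, and add each patient's mean ppFEV1 over the prior year as a second continuous covariate. Include the prior-year mean in the propensity score.
- Make the prior-year-anchored ESS-versus-CMT comparison a named, pre-specified sensitivity analysis. It complements the covariate: under the assumptions above it removes the dip bias, where the covariate leaves about 0.4 of 2 points with four prior values and about 1 with one, but it is more exposed to differing underlying decline.
- Before follow-up is examined, compare the groups on enrolment ppFEV1 minus prior-year mean, and report the estimate with its confidence interval. With few or noisy prior values a non-significant result is no reassurance. A group-by-time fit to pre-enrolment values alone would not serve, because the dip lies in the enrolment value.
- Use prior values on the same modulator regimen as at enrolment where available. Where they are missing, model the pre-enrolment values jointly instead of using a missing indicator.

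The cost is analysis-plan wording, one covariate and abstraction of routine spirometry that the plan already intends to use. The downside is uneven availability. The exclusion covers only modulator starts or changes within 90 days of enrolment, so a recent starter may have as little as about three of the twelve prior months on the current regimen, and some patients will have few or no usable prior values.

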### Outcome assessments

To address objective 1, primary pulmonary outcome measure will be ppFEV_1_. Absolute values of FEV1 and FVC will be assessed as secondary spirometry measures, enabling evaluations of the FEV1/FVC ratio [17]. Forced expiratory flow at mid-lung volume (FEF25-75) is an important marker of small airway disease and will also be evaluated [18]. Secondary outcomes include the frequency of PEx (both outpatient and inpatient) and intravenous (IV) and oral antibiotic use. PEx will be defined by the Rosenfeld criteria [19]. The number of PEx, number of hospitalizations, and days of IV and oral antibiotics used will be tracked.

To address objective 2, quality of life outcome measures will include CFQ-R, evaluating CF-specific QOL [20], and the SNOT-22, evaluating QOL in subjects with CRS [21]. PHQ-9-revised will be used for depression screening [22], and the PSQI will measure sleep duration and quality [23]. CFQ will be used for cognitive assessment [24]. The HIT-6 will be utilized to determine headache severity [25]. For evaluation of olfactory function, we will use patient-reported and objective olfactory function tests. The QOD will assess the impact of olfactory dysfunction [26]. The SIT is a measure of objective olfactory function and complements the patient-reported QOD survey [27].

To address productivity loss and health utility in objective 3, the WPAI will be used to assess the impact of a specific health problem on normal work/school or daily activity [28]. Health utility value (HUV) will be quantified from the EQ-5D [29].

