### Statistical power and sample size

Sample size and power were calculated using software G Power (v. 3.1). Type I error will be controlled at two-sided 5% level. Sample size calculations were initially based on our primary QOL outcome measure (SNOT-22 scores) for objective 2, given strong evidence of improvements in the literature [33]. This was then applied to objective 1. For objective 2, detecting SNOT-22 score changes pre- and post-12 months ESS requires 9 patients for 80% power. To determine changes between treatment groups over time, considering a potential 30% cross-over between ESS and CMT groups, 106 patients are needed for 80% power, as indicated by prior data [34]. Accounting for 20% potential dropouts, our recruitment target is 150 participants, with an anticipated enrollment of approximately 170 across all centers.

Regarding ESS effects on ppFEV_1_, previous mixed results complicate clear expectations to use in power calculations for objective 1. Assuming 170 participants (factoring in 20% dropout), we will have 80% power to detect a 1.6% ppFEV_1_ change for objective 1 and a 2.3% ppFEV_1_ change for objective 1 accounting for HEMT.

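### The default Poisson model for exacerbations and antibiotic use names no handling of overdispersion; for antibiotic days its standard errors would foreseeably be far too small

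*Protocol article*

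**What the plan says.** Under Statistical methods, the Objective 1 paragraph specifies the analysis as "Using a generalized linear model with a Poisson distribution and prior year data", and continues "we will assess the impact of ESS versus CMT on exacerbation rates and antibiotic use". One model therefore serves both outcomes, and it is the only model named for them. The same section opens with a general commitment: "For all objectives, we will verify predictive model assumptions and test goodness-of-fit, considering alternative models if needed". It does not say what finding would trigger a change or what the replacement would be.

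Under Outcome assessments these outcomes are secondary ("Secondary outcomes include the frequency of PEx (both outpatient and inpatient) and intravenous (IV) and oral antibiotic use"); ppFEV1 is the primary pulmonary measure. On what is recorded, that section says "The number of PEx, number of hospitalizations, and days of IV and oral antibiotics used will be tracked". Table 2 under Objectives & endpoints lists "Rate of PEx, and antibiotic utilization for exacerbations compared between treatment groups". The sample-size section states "Type I error will be controlled at two-sided 5% level". The article gives no event rate, dispersion or power for exacerbations or antibiotic use.

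**The concern.** A Poisson model fixes the variance at the mean. Its model-based standard errors are right only if that holds.

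The two outcomes differ in how likely it is to fail. Exacerbation counts are overdispersed to the extent that patients differ in underlying rate. Some such variation is likely here, because the plan's own covariates span FEV1 strata from above 80% to below 50% predicted, and modulator use varies. Antibiotic days fail for a structural reason: one decision to treat adds a block of days at once, so days are not independent single events.

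At stake are intervals that are too narrow and spurious differences between surgery and medical therapy, in either direction, on two outcomes listed beside ppFEV1 under Objective 1. The general promise to check fit may catch this. But the replacement would then be chosen after seeing the data, in a non-randomised comparison, for a failure that can be foreseen now.

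**Working it through.** **Inputs from the article.** Two-sided alpha is 0.05. The recruitment target is 150, with about 170 anticipated and 20% dropout, so 150 × 0.8 = 120 to 170 × 0.8 = 136 evaluable. Follow-up is 12 months.

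**Assumptions (no figures in the article).** Exacerbation rate 0.5 to 1.5 per year; gamma frailty between patients with variance k of 0.5 to 1, and k = 0 for comparison; antibiotic courses of 5 or 14 days in the formula and 10 to 21 days in the simulation; equal group sizes.

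**Step 1: formula.** If variance = φ × mean, a nominal 5% Wald test with model-based Poisson errors has actual type I error 2 × [1 − Φ(1.96/√φ)]. At φ = 1 this gives 5.0%, the plan's own level.

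| φ | Type I error |
|---|---|
| 1 | 5.0% |
| 1.5 | 11.0% |
| 2 | 16.6% |
| 5 | 38.1% |
| 10 | 53.5% |
| 14 | 60% |
| 20 | 66.1% |

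**Step 2: φ for antibiotic days.** Let courses arrive as a Poisson process with mean m, each lasting L days. The mean number of days is L·m and the variance is L²·m, so φ = L with no patient heterogeneity at all. Five-day courses give φ = 5 and 38%; 14-day courses give φ = 14 and 60%. If course length varies, φ = E(L²)/E(L). For lengths uniform on 10 to 21 days the mean is 15.5 and the variance 143/12 = 11.9, so φ = (15.5² + 11.9)/15.5 ≈ 16.3. Frailty adds to this.

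**Step 3: φ for exacerbation counts.** With gamma frailty, φ = 1 + m·k. At m = 1 and k = 1, φ = 2. At k = 0, φ = 1 and there is no inflation.

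**Step 4: simulation under no treatment effect.** A Poisson GLM was fitted with and without log(prior-year count + 0.5) as covariate. There were 1,500 runs per setting for counts (N = 120 and 136) and 1,000 for days (N = 120).

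| Outcome | Without prior-year covariate | With prior-year covariate |
|---|---|---|
| Exacerbations, k = 0 | 4% to 6% | 4% to 5% |
| Exacerbations, k = 0.5 to 1 | 7% to 22% | 6% to 13% |
| Days, k = 0 | 62% to 64% | 61% to 64% |
| Days, k = 0.5 to 1 | 66% to 76% | 67% to 70% |

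Estimated φ for days ran from about 16 to 39, and about 16.2 at k = 0, in line with Step 2. The prior-year covariate roughly halves the excess for exacerbations at the higher rates and frailty, but barely helps for days.

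**Step 5: remedy.** In the same simulations, type I error was 3.7% to 6.3% with quasi-Poisson (Pearson-scaled) errors and 4.2% to 6.5% with robust (HC1) errors, for counts and days alike.

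**The case against.** The strongest reply is that the plan is not tied to a plain Poisson model. It commits, for all objectives, to check assumptions and fit and to consider alternatives, and overdispersion is the standard check for this model. That stands, and it rules out saying that the study will report false differences at the rates above. It does not remove the point: a check suits a model that might fail, whereas for days the failure follows from how days accumulate.

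Second, the modelling sentence refers to antibiotic use and does not say days. That also stands, so the 38% and 60% are conditional. Still, days are the only antibiotic measure named under Outcome assessments, so this is the natural reading.

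Third, a reader might infer that exacerbation counts are as badly affected. The article does not support this. It brings prior-year data into the model, and with a prior-year covariate the inflation is moderate under the assumed range and vanishes without overdispersion.

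Fourth, a reader might infer that prior-year and follow-up counts are stacked as independent rows, or that no person-time offset is planned. Neither is stated. The wording fits a prior-year covariate equally well, rates are what is to be modelled, and a condensed article may leave such details to the full plan.

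Finally, the outcomes are secondary, and the 5% statement sits in a sample-size section that does not power them. This limits the weight of the point.

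**Conclusion.** The point holds in limited form. The protocol names a Poisson default for two unlike secondary outcomes and leaves overdispersion to an unspecified alternative.

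- **Antibiotic days with model-based errors:** type I error of about 38% (5-day courses) to 60% (14-day courses) against a stated 5%, with no patient heterogeneity needed. The course length is an assumption, but any multi-day course inflates the error.
- **Exacerbation counts:** about 6% to 13% with a prior-year covariate and 7% to 22% without. These rest on assumed rates of 0.5 to 1.5 per year and frailty variance of 0.5 to 1; there is no inflation at φ = 1.

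The primary ppFEV1 mixed model is untouched. This should be fixed before analysis, but it does not threaten the study's main comparison.

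**What to change.** Name the handling of overdispersion in advance:

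- **Exacerbations and antibiotic courses:** negative binomial regression, or Poisson regression with robust or quasi-Poisson standard errors, with log follow-up time as offset and the prior-year count as covariate.
- **Antibiotic days:** a separate analysis with robust or bootstrap standard errors.

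The general goodness-of-fit commitment can stay as a further safeguard.

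The cost is analysis wording and wider intervals. On the log-rate scale they widen by about √φ: √5 ≈ 2.2 and √14 ≈ 3.7 times for days in the examples above, and √1.5 ≈ 1.2 times for counts at φ = 1.5. Analysing courses also requires that course starts can be identified from the antibiotic records, which the article does not state.
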